#### Rochester epidemiology project

The development and use of the REP have been described in detail [142–145]. In brief, the REP is a medical records linkage system that allows detailed collection of data on a well-defined population (Olmsted and surrounding Counties, Minnesota, US) starting in the early 1960s. The REP was developed with the recognition that nearly all residents of Olmsted County received their medical care at one of two hospitals and/or at affiliated institutions because of the central location of the hospitals in an area in which there are no other competing medical centers. In addition, other small private practices have partnered with the major medical centers in the area to contribute to the REP. As such, population estimates for the Olmsted County by REP are slightly higher and more comprehensive than those reported in the US Census (1970, 104.1%; 1980, 103.5%; 1990, 102.4%; and 2000, 102.7% of the US Census counts) [144]. The characteristics of the population are similar to those of residents from the Upper Midwest of the US [145, 146]. The records contain details of every inpatient hospitalization at the affiliated hospitals, every outpatient visit to the office, clinic, or emergency department, as well as every laboratory result and correspondence concerning each patient. The medical records are easily retrievable because the REP has maintained extensive indices based on clinical and histologic diagnoses (i.e., diagnosis codes) and surgical procedures. The result is the linkage of medical records from nearly all sources of medical care utilized by the Olmsted County population. Each year, more than half of the population is examined at one of the REP facilities, and about 85–100%, depending on the age group, have at least one REP contact over a 3-year period [142].

The REP represents the same geographical region as both the UMN and Mayo LDs with the same time frame starting in the 1960s, making it an ideal control group (reference cohort) for long-term follow-up.

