#### Initial matching algorithm

After finalizing the list of exclusionary codes, up to 4 potential controls were identified for every donor. All controls were residents of Olmsted County (or surrounding counties) at some point and lacked any exclusionary diagnoses before the index date (date of donation for the matched LD) or up to 1 year after the index date. The 1-year window after the index date was used because some diseases may be present on the index date but not diagnosed due to the intermittent nature of clinic visits in the medical record. This matching was accomplished first for the UMN donors and then for the Mayo Clinic donors. These potential REP controls were initially identified based on the following requirements: (1) Olmsted County or surrounding county resident at index date, (2) at least one REP encounter prior to index and at least one REP encounter one year or more after index, (3) age difference between LD and potential REP control at index less than 5 years, and (4) exact match on broad racial categories (Black vs. non-Black). If more than four controls meet these criteria, the four best controls based on (1) exact match on more granular racial categories (White or unknown, Black, Asian, Hawaiian/Pacific Islander, Other), (2) exact match on ethnicity (Hispanic, non-Hispanic), and (3) minimum difference in age at index was selected. If fewer than four controls were identified, the matching criteria were broadened to allow for unknown county of residence at the index date and subsequently known non-resident of Olmsted or surrounding counties at the index date. The full algorithm is provided in Fig. 2. From this initial algorithmic matching over 16,000 and 14,000 potential controls were identified for the UMN and Mayo Clinic donors, respectively.

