#### Control validation and medical record abstraction

Subsequently, all identified potential control charts (paper and electronic) are being manually reviewed and abstracted into a REDCap database by the abstraction team, which consists of a nurse practitioner who previously worked in a kidney transplant clinic, nurses, and medical research trainees. Abstraction guidelines with screenshots of the database are maintained and updated as needed for use by all abstractors. After orientation is completed, each abstractor completes a set of 20 cases to ensure consistency with these guidelines. Chart abstraction involves two steps: (1) validation of the potential control (i.e., ensuring that the subject would have been a suitable donor at the index date), and then, if valid: (2) capturing clinical and laboratory data. The validation step involves reviewing medical records prior to the index date for contraindications for kidney donation. The following conditions are often found by abstractors resulting in exclusion of possible control: hypertension (blood pressure over 140/90 mm Hg), Proteinuria (1 + dipstick, 24-hour urine protein > 200 mg, protein osmolarity ratio > 0.42), impaired kidney function (creatinine > 1.3 mg/dL in men, > 1.1 mg/dL in women), non-tobacco substance abuse (interferes with lifestyle or requires hospitalization/treatment), obesity (BMI > 40 kg/m^2^), history of recent cancer (other than non-melanoma skin cancers), severe depression/anxiety (untreated and interferes with lifestyle), history of urological abnormalities (significant structural/functional abnormalities of the urinary tract), heart disease, liver disease, and chronic obstructive pulmonary disease.

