We will also evaluate if the effect of donation differs across baseline characteristics (i.e. evaluate if a characteristic modifies the effect of donation) by testing the significance of the interaction term between donation and the characteristic in the model. These models will also allow us to assess the attributable risk of donation in LDs with certain characteristics at donation. We will specifically assess if age, BMI, smoking, donation eGFR, and race/ethnicity modify the effect of donation on ESKD and mortality. As a sensitivity analysis, the analyses will be repeated using a subset of REP controls having at least 5 years of medical history preceding the index date.

Logistic regression models fit using generalized estimating equations will be used to test for differences in the odds of gestational hypertension and preeclampsia between LDs and controls for all pregnancies occurring after the index date, while accounting for women having potentially multiple pregnancies. Adjustment variables to be considered in the model include: race/ethnicity, age at pregnancy, gravidity, and previous occurrence of pregnancy complications. Secondary analyses using logistic regression models will test for differences in the odds of these complications in the first pregnancy after the index date, adjusting for having previous pregnancies, and second pregnancy after the index date, adjusting for the occurrence of pregnancy complications in the first post-index date pregnancy.

A linear mixed effects model will be used to test the difference in the trajectory of eGFR over time between living LDs and healthy controls. This model will initially have a linear effect for time with subject-specific random intercepts and slopes, but natural splines will be used to investigate nonlinear temporal trajectories.

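### Controls can count as healthy at index without having been seen near it, and the planned 5-year-history sensitivity analysis tests length of record, not recency

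*Protocol article*

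**What the plan says.** All of this is in the protocol article.

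- **Initial matching algorithm.** A potential control needs "at least one REP encounter prior to index and at least one REP encounter one year or more after index". Neither encounter has an outer time limit. Controls must have "lacked any exclusionary diagnoses before the index date (date of donation for the matched LD) or up to 1 year after the index date". The year after index is included because "some diseases may be present on the index date but not diagnosed due to the intermittent nature of clinic visits". If fewer than four controls are found, the criteria widen to "allow for unknown county of residence at the index date and subsequently known non-resident of Olmsted or surrounding counties at the index date".
- **Rochester epidemiology project.** "Each year, more than half of the population is examined at one of the REP facilities", and about 85–100%, depending on age group, "have at least one REP contact over a 3-year period".
- **Control validation and medical record abstraction.** Every potential control's chart is reviewed by hand. "The validation step involves reviewing medical records prior to the index date for contraindications for kidney donation". The nearest measurements before and after index are also recorded as baseline, but no exclusion based on the later ones is stated.
- **Primary control group and matching algorithms.** The primary set needs BMI, blood pressure, antihypertensive use and smoking to be ascertainable. It also needs a normal creatinine, blood urea nitrogen or urine protein from the 10 years before index, with no abnormal value. Under age 50 a normal urine protein is enough. No glucose test is required.
- **Control groups for sensitivity analysis.** Groups (ii) and (iii) exclude known abnormal kidney function but do not require a kidney test. Group (iii) also drops the clinical characteristics.
- **Statistical analyses details.** The analyses are to be repeated in "a subset of REP controls having at least 5 years of medical history preceding the index date".

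**The concern.** The aim is to find people who could have donated on the matched donor's date. For a donor, health on that date was established by a full work-up. For a control it is inferred from the record, and a record with no entries near index reads the same as a record of good health.

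The year after index is meant to catch disease that was present but not yet diagnosed. It can do so only if the person is seen in that year, and no such visit is required. The later encounter that is required falls when the period has ended, so disease found there no longer excludes the control. It becomes a post-index event. Hypertension, diabetes, proteinuria, chronic kidney disease and cardiovascular disease are all analysed as outcomes after index.

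The error falls on controls and not on donors. It raises apparent incidence in controls and pulls the comparison toward no difference, which is also the direction of the study's hypothesis that any excess is clinically insignificant.

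**Working it through.** The article gives no figure for this point, so there is none to reproduce. The check has three steps.

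**1. Do the rules together close the gap?** Take a hypothetical resident aged 40. The last visit was 8 years before index, with normal urine protein, BMI and blood pressure recorded and smoking status known. The next visit is 3 years after index, when hypertension that began before index is found.

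| Rule | Result |
|---|---|
| One encounter before index | met (8 years earlier) |
| One encounter a year or more after index | met (year 3) |
| No exclusionary diagnosis up to 1 year after index | met (no visit, so no diagnosis) |
| Chart review of pre-index records | nothing to find |
| Primary set: normal kidney test within 10 years | met |
| Sensitivity subset: 5 years of history | met (8 years) |

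This person passes every stated rule and contributes a hypertension event at year 3. The 5-year subset does not help, because a long record can still end long before index.

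**2. How often can the year be empty?** From the contact rates in the Rochester epidemiology project section:

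- not examined in a given year: below 1 − 0.50 = 0.50, so up to just under half
- no contact over 3 years: 1 − 1.00 = 0 to 1 − 0.85 = 0.15

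The two rates agree. If years were independent, a yearly probability of 0.50 gives 1 − (1 − 0.50)³ = 0.875 over 3 years, inside the stated range.

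**3. What could it do to a risk ratio?** This is an illustration only. Assumed inputs:

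- undiagnosed disease at index, u = 1–5%
- controls with no visit in the year, m = 30–50%
- true donor-to-control risk ratio, 1.20

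The control risk c = 8–14% is borrowed, for scale, from the range that the Power section gives for eGFR < 45.

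Share of controls carrying missed disease: a = u × m, from 0.01 × 0.30 = 0.3% to 0.05 × 0.50 = 2.5%. An intermediate case is 0.02 × 0.50 = 1.0%.

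Observed ratio = 1.20 × c / (c + a):

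| a | c = 8% | c = 14% |
|---|---|---|
| 0.3% | 1.20 × 0.08/0.083 = 1.16 | 1.20 × 0.14/0.143 = 1.17 |
| 1.0% | 1.20 × 0.08/0.090 = 1.07 | 1.20 × 0.14/0.150 = 1.12 |
| 2.5% | 1.20 × 0.08/0.105 = 0.91 | 1.20 × 0.14/0.165 = 1.02 |

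For scale, the Power section's detectable hazard ratios for eGFR < 45 run from 1.15 to 1.25. The calculation leans high. It supposes that any visit in the year would have revealed the disease, that all missed disease surfaces later, and that carriers of old disease still count among those at risk.

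**The case against.** The strongest reply is that the one-encounter rule defines only the initial pool. A reader might infer that the analysed controls need nothing more. They do: all charts are validated by hand, and the primary set requires clinical data and a normal kidney test. This stands, and it reduces the problem, most of all for kidney outcomes. It does not remove it, since the test may be 10 years old, chart review looks back from index, and a kidney test does not exclude diabetes or cardiovascular disease.

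Second, the Primary control group section names the conflict openly. Including people without laboratory values risks detection bias, and requiring values risks selection bias. Several control cohorts are planned to span the two. This also stands, and it is why a hard recency rule for primary eligibility is not warranted. But that discussion concerns missing laboratory values, not gaps between visits, and none of the planned cohorts varies recency of contact. The cancer comparison is a useful general check on selection, but it is not aimed at silent hypertension or diabetes.

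Third, the contact rates describe the whole population. A reader might infer that nearly half of the controls have an empty year. The article does not support that: controls are chosen for having encounters on both sides of index, so their visit pattern may differ.

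Fourth, a reader might divide the 301 donors with diabetes in the Power section by 4022 (7.5%) and scale the bias to that. The 301 are only those who developed diabetes without earlier cardiovascular disease, and they are donors, so this is not the control incidence of diabetes.

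Finally, the article refers to Fig. 2 for the full algorithm, and neither that figure nor the abstraction guidelines are shown here. A recency rule could be stated there.

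**Conclusion.** The concern holds in a limited form. As the text stands, potential controls may have a single pre-index encounter of any age, and nothing requires a visit in the year that is meant to reveal undiagnosed disease. The later safeguards shrink the gap without closing it. It is widest in sensitivity groups (ii) and (iii) and among controls admitted by the residence fallback, for whom the quoted contact rates cannot be assumed.

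The outcomes exposed are hypertension, diabetes, chronic kidney disease and cardiovascular disease, with bias toward hiding donor risk. It would go too far to extend this to the mortality and ESKD comparisons, which rest largely on the National Death Index and the United States Renal Data System and depend little on when a clinic visit happened.

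The size cannot be derived from the article. The illustration shows that it could range from slight to enough to mask a 20% excess, but the prevalence and visit shares are assumed. This is a cheap improvement to a planned sensitivity analysis, not a flaw that invalidates the primary comparison.

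**What to change.** Keep primary eligibility as planned. Change the sensitivity analysis in Statistical analyses details as follows:

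1. Define the subset as controls with at least 5 years of history **and** at least one REP encounter within 3 years before index. Both conditions use pre-index information only.
2. Rerun the match inside the subset, and drop donors left without a control.
3. Report the change in the donor-control comparison for hypertension, diabetes, chronic kidney disease and cardiovascular disease.

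**Cost.** The recency condition is a filter on encounter dates already held, plus one further matching run. By the 3-year contact rate it loses about 0–15% of resident controls, and probably more among non-residents. It would lose more still if a recorded blood pressure were required, because the 85–100% figure counts any contact. The earliest index years will also lose controls, since the REP starts in the early 1960s and 5 years of history may not exist. By Table 1, donors from the 1960s number 99 + 45 = 144 of 4022 + 3035 = 7057, or 2.0%. The subset will lean toward people who use care, which is the selection bias that the article warns of, so it belongs beside the primary result and not in its place.

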**Fig. 2 Fig2:**
[figure not shown]
REP Control Match Flow Chart

#### Control validation and medical record abstraction

Subsequently, all identified potential control charts (paper and electronic) are being manually reviewed and abstracted into a REDCap database by the abstraction team, which consists of a nurse practitioner who previously worked in a kidney transplant clinic, nurses, and medical research trainees. Abstraction guidelines with screenshots of the database are maintained and updated as needed for use by all abstractors. After orientation is completed, each abstractor completes a set of 20 cases to ensure consistency with these guidelines. Chart abstraction involves two steps: (1) validation of the potential control (i.e., ensuring that the subject would have been a suitable donor at the index date), and then, if valid: (2) capturing clinical and laboratory data. The validation step involves reviewing medical records prior to the index date for contraindications for kidney donation. The following conditions are often found by abstractors resulting in exclusion of possible control: hypertension (blood pressure over 140/90 mm Hg), Proteinuria (1 + dipstick, 24-hour urine protein > 200 mg, protein osmolarity ratio > 0.42), impaired kidney function (creatinine > 1.3 mg/dL in men, > 1.1 mg/dL in women), non-tobacco substance abuse (interferes with lifestyle or requires hospitalization/treatment), obesity (BMI > 40 kg/m^2^), history of recent cancer (other than non-melanoma skin cancers), severe depression/anxiety (untreated and interferes with lifestyle), history of urological abnormalities (significant structural/functional abnormalities of the urinary tract), heart disease, liver disease, and chronic obstructive pulmonary disease.

Similar to the donor candidate assessment, certain conditions are allowed for controls at the time of index if they are otherwise healthy. A BMI of 35–40 kg/m^2^ is allowed if the control is deemed to be in otherwise very good health as BMIs in this range are allowed in some donors. As with donors, medically well-controlled hypertension is allowed in controls over 50 years of age. Controls on more than 1 non-diuretic antihypertensive medication or more than 1 diuretic antihypertensive medication are excluded. Depression/anxiety is allowed if well controlled, infrequent, and acute episodes had occurred in the distant past relative to the index date. Substance abuse is also allowed if use was in the remote past; current marijuana and alcohol use is allowed as long as it does not interfere with work and social function. Patients who were pregnant at the index date or within 3 months postpartum, or hospitalized within 2 weeks of index date (for a non-exclusionary reason), may be rematched to a different donor at a different index date.

If it is unclear if a certain control would have been eligible to donate given their medical history, a review by kidney donation experts (Drs. [name], [name], and [name]) is used to approve or exclude the potential control. The abstraction guidelines are subsequently updated to ensure future consistency. In addition, the abstractor team meets monthly after completing a reliability chart (same chart for each abstractor) to ensure similar abstractions among the abstractor team.

If a control is validated, abstractors proceed to collect additional baseline and follow-up data. This includes any mention of family history of DM, hypertension, CKD, or ESKD. We obtain the closest laboratory data measures before and after the index date for baseline. These measures include: height, weight, blood pressure (avoiding blood pressure obtained during visits to the emergency department), serum creatinine, blood urea nitrogen (BUN), serum glucose, urine glucose, and any assessment of proteinuria/albuminuria (avoiding those with concurrent urinary tract infections).

### Outcomes

Outcomes include mortality, CVD and cardiovascular mortality, serial creatinine (to determine eGFR trajectory and chronic kidney disease) and other laboratory measures, pregnancy outcomes and complications, and development of diseases that frequently lead to CKD (e.g., hypertension, DM, and obesity). Outcomes will be ascertained from national registries, medical record review of donors and REP controls, and a new survey administered to both donors and controls. A list of data collected, data source, and frequency of data collection is provided in Table 2 and is summarized below.

**Table 2 Tab2:** Data collection sources and frequency for REP controls and UMN donors. CR: Chart Review, DS: Donor survey + chart review if available (every 3 years), SS: Study Survey, LD: Lab data (every year)

	Source of data	
Data	UMN Donors	REP Controls
**Baseline characteristics**		
Demographics	CR	CR^1^
History of substance abuse^2^	CR	CR
Diagnosis of Depression/Anxiety Disorder^3^	CR	CR
High cholesterol	CR, SS	CR, SS
Hypertension^4^	CR, SS	CR, SS
Family history of kidney disease, DM, HTN	CR, DS, SS	CR, SS
Smoking history	CR, DS, SS	CR, SS
**Lab measurements**	Requested every 3 years with study survey	Recorded every year if available
BUN/Urea	CR	CR, LD
Glucose	CR	CR, LD
Urine protein^5^	CR	CR, LD
BMI	CR, DS, SS	CR, LD, SS
Creatinine	CR, DS, SS	CR, LD, SS
Blood pressure	CR, DS, SS	CR, LD, SS
**Outcomes**		
CVD^6^	DS, SS	CR, SS
Diabetes	DS, SS	CR, SS
Cancer	DS, SS	CR, SS
Hematuria	DS, SS	CR, SS
High cholesterol treated with medication	DS, SS	CR, SS
Hypertension treated with medication	DS, SS	CR, SS
Pregnancy history^7^	DS, SS	CR, SS
Proteinuria	DS, SS	SS
Kidney disease/ abnormal kidney function/ ESKD	DS, SS, USRDS	CR, SS, USRDS
Vital status and cause of death	DS, SS, NDI	CR^8^, SS, NDI

^1^ Chart review for controls includes abstraction of data from electronic transfer from the Rochester Epidemiology Project (REP) database, Mayo clinic paper records, Olmstead Medical Center electronic and paper record, Olmstead Community Hospital electronic and paper records, Epic, and the REP browser (electronic record system) from date of first REP encounter to date of last follow-up

^2^Permissible substance abuse at donation/donation is defined as a remote history of marijuana use with no active use around the time of the donation date or current marijuana use as long as it does not interfere with lifestyle. Remote other substance use is not a contraindication to donation as long as its truly remote

^3^Permissible depression/anxiety at donation/donation is defined as well controlled, in the distant past prior to the donation date, or involving few episodes of care

^4^Permissable hypertension at donation/donation includes that which is well controlled (< 140/90), treated with a diuretic antihypetensive agent, a non-diuretic antihypertensive agent, or both (1 diuretic and 1 non-diuretic hypertensive agent), age needs to be > 50 years. Exclude if age < 50 years or not well controlled or using 2 or more non-diuretic agents or using 2 or more diuretic agents

^5^Urine Dipstick, 24 H Urine Protein, Urinalysis Predicted 24-Hour Protein, Protein-Osmolality Ratio, Urine Protein to Creatinine Ratio, Urine Albumin to Creatine Ratio, 24 H Urine Albumin

^6^Congestive heart disease, myocardial infarction, cerebrovascular accident, transient ischemic attack, angioplasty, stents

^7^Number and year of pregnancies, pregnancy outcome (singleton, twins, triplets, ≥ 4, abortion, miscarriage, fetal death), gestational length (full term, pre-term), and pregnancy complications (gestational hypertension, gestational diabetes, proteinuria, eclampsia, preeclampsia)

^8^Proof of life noted for medical encounters with no data

